### Pilot research program eligibility

Eligibility criteria included the following: (1) scheduled for a WNP; (2) willingness to complete surveys at 0, 6, and 12 months; (3) willingness and ability to self-report weight data by text message; and (4) willingness to receive outreach from the study team in response to text messaging data. Exclusion criteria are the inability to read or write English.

### Pilot research program eligibility

Eligibility criteria included the following: (1) scheduled for a WNP; (2) willingness to complete surveys at 0, 6, and 12 months; (3) willingness and ability to self-report weight data by text message; and (4) willingness to receive outreach from the study team in response to text messaging data. Exclusion criteria are the inability to read or write English.

### Recruitment

Patients will be referred to the WNP by PCPs. All patients scheduled for a WNP appointment will be eligible for participation in a single-arm, 12-month pilot study. We anticipate that the Weight Navigator will see approximately 4 patients per 4-h clinic session once per week. Accounting for vacations, holidays, and canceled appointments, we estimate that the Weight Navigator will see approximately 150 patients during the first year of the program.

All patients scheduled for a WNP appointment will be eligible for participation in a single-arm, 12-month pilot research study. A research project manager will contact scheduled patients by telephone at least 5 days prior to their appointment date to invite them to participate in research and describe the study processes. Individuals who desire to participate in research will complete an online informed consent document and the baseline survey prior to the WNP appointment using the RedCap survey platform (REDCap, n.d.). Recruitment will continue until we reach our target of 30 participants.

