#### Feasibility and acceptability of the WNP

Consistent with recommendations for conducting pilot studies (Eldridge *et al.*, 2016), our primary outcomes will be measures of feasibility (ie, extent to which an innovation can be successfully used in a given setting) and acceptability (ie, stakeholder perception that an innovation is satisfactory). Measures of WNP feasibility will include rates of (1) referral (ie, number of patients referred to the WNP divided by the number of patients eligible for the program, as determined by data extraction from the EHR) and (2) uptake (ie, number of patients referred to the program divided by the number of individuals who complete a WNP appointment).

We will assess WNP intervention acceptability through semi-structured interviews with a purposive sample of WNP research program participants to explore individuals’ experiences with the program and solicit feedback on opportunities for improvement. We will also survey primary care providers and patients regarding their satisfaction with the program and solicit feedback on opportunities for improvement.

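### The primary uptake measure pools patients who get a pre-visit research call with patients who do not, so it may not represent routine use; the direction and size are not known from the protocol.

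*Protocol article*

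**What the plan says.** The section on feasibility and acceptability of the WNP states that "our primary outcomes will be measures of feasibility" and acceptability. Uptake is one of the two WNP feasibility rates named there. It is defined as "number of patients referred to the program divided by the number of individuals who complete a WNP appointment", over all patients, with no separation by research contact or by period.

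The Recruitment section places research contact ahead of the event that uptake counts: "A research project manager will contact scheduled patients by telephone at least 5 days prior to their appointment date". The purpose of the call is "to invite them to participate in research and describe the study processes". Patients who wish to take part "will complete an online informed consent document and the baseline survey prior to the WNP appointment". The section also says "Recruitment will continue until we reach our target of 30 participants", and separately "we estimate that the Weight Navigator will see approximately 150 patients during the first year of the program".

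The Intervention section describes the routine pre-visit contact. A clinical scheduler contacts each eligible referred patient to book the visit and sends a weight history questionnaire through the portal. The research call comes on top of this.

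**The concern.** A pilot measures uptake so that others can judge whether patients will attend when the program runs without a study around it. Here, some patients have a conversation with research staff about the coming appointment, and some also complete consent and a survey, before they decide whether to attend. Routine patients would have none of this.

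The research contact is tied to a target of 30, well below the expected 150, so the natural reading is that an early group is called and a later group is not. One pooled ratio then describes neither situation. If the call changes attendance, the uptake figure carried into the planned large pragmatic trial, and into any decision to scale the program, partly reflects contact that will not exist there. The limitations section recognises that some components depend on research funding, but its example is the text-messaging outreach, not the pre-visit call.

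**Working it through.** **Inputs from the protocol.** Target of 30 research participants; about 150 patients seen in year 1; capacity of "approximately 4 patients per 4-h clinic session once per week"; call made before the visit; uptake not split by contact.

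**The plan's own figure.** 4 patients × 52 weekly sessions = 208 visits before allowances. 150 ÷ 4 = 37.5 sessions, and 150 ÷ 208 = 72% of capacity. The allowance for vacations, holidays and cancellations is not quantified, so 150 is plausible but cannot be reproduced exactly.

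**Assumed inputs (none is in the protocol).** Consent rate among those called, c: 20% to 75%. Attendance among scheduled patients, a: 60% to 90%. Change in attendance caused by the call, d: -5 to +15 points, including zero.

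**Formulas.**
- Patients called until 30 consent = 30 ÷ c
- Patients scheduled = 150 ÷ a
- Share called, f = (30 ÷ c) ÷ (150 ÷ a)
- Shift in pooled completion among scheduled patients = f × d

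| c | a | called | scheduled | f | d = -5 | d = 0 | d = +5 | d = +10 | d = +15 |
|---|---|---|---|---|---|---|---|---|---|
| 75% | 60% | 40 | 250 | 0.16 | -0.8 | 0 | +0.8 | +1.6 | +2.4 |
| 50% | 75% | 60 | 200 | 0.30 | -1.5 | 0 | +1.5 | +3.0 | +4.5 |
| 30% | 75% | 100 | 200 | 0.50 | -2.5 | 0 | +2.5 | +5.0 | +7.5 |
| 20% | 90% | 150 | 167 | 0.90 | -4.5 | 0 | +4.5 | +9.0 | +13.5 |

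The first and last rows are the extremes of the assumed grid. In the last row nearly everyone is called. Mixing is then slight, but the uptake figure is measured almost wholly under research contact, which is no better for judging routine use.

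**Dilution to the protocol's denominator.** Uptake is defined over referred patients, whereas the call reaches only those already scheduled. If a fraction s of referred patients is scheduled, the shift in uptake is s × f × d. With s assumed at 60% to 80%, d = +5 gives 0.60 × 0.8 = 0.5 to 0.80 × 4.5 = 3.6 points. d = +15 gives 0.60 × 2.4 = 1.4 to 0.80 × 13.5 = 10.8 points. d = -5 gives -0.5 to -3.6 points.

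**Comparison with sampling error.** The 95% half-width for completion among scheduled patients is 1.96 × √(0.75 × 0.25 ÷ 200) = 6.0 points for 150 of 200, and 1.96 × √(0.60 × 0.40 ÷ 250) = 6.1 points for 150 of 250. Most cells in the table are smaller than this.

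**Direction of the ratio as printed.** The uptake ratio is written as referred over completed. With 250 referred (illustrative), 150 completed gives 250 ÷ 150 = 1.67, and 160 completed gives 250 ÷ 160 = 1.56, so better attendance lowers it. The evidently intended ratio moves the other way: 150 ÷ 250 = 0.60 and 160 ÷ 250 = 0.64. The shifts above refer to the intended ratio.

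**The case against.** A reader might infer that uptake is overstated, because a telephone call about a coming visit works as a reminder. The protocol does not support that as a finding. The stated purpose of the call is a research invitation, and it could raise attendance, leave it unchanged, or put off patients who dislike the research burden. The five days are a minimum lead time with no upper limit, so the call need not fall close to the visit. A reader might also count the month-0 interview as pre-visit contact, but only consent and the baseline survey are placed before the appointment.

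Other objections carry weight:
- The contrast with routine care is narrow, since the scheduler's contact and the questionnaire are part of the routine process.
- The effect on a per-referral rate is diluted, and it may be smaller than sampling error.
- No threshold for uptake is stated, so no stated decision turns on a few points.
- Making patients seen after recruitment closes the headline would confound call status with program start-up. That group could be very small: at 20% consent and 90% attendance, 167 - 150 = 17 scheduled patients.

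It can also be said that a condensed article leaves breakdowns to fuller documents. That does not remove the point. The article itself fixes both the recruitment procedure and the uptake definition, and it is their combination that clouds the measure. What stands from the other side is that the direction must be left open and the remedy must be descriptive.

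**Conclusion.** The pooling follows from the plan. A non-program contact precedes the attendance that a primary measure counts, it is linked to a target of 30 against about 150 expected patients, and the measure is not split. That calls stop at 30 is an inference from the recruitment rule, though a natural one. Uptake may therefore not represent routine use.

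Neither the sign nor the size of the distortion can be settled from the protocol, and a statement that uptake is biased upward goes beyond it. The shift is upward if the call acts as a reminder, nil if it has no effect, and downward if it deters. Over the assumed ranges it runs from -4.5 to +13.5 points among scheduled patients, and is smaller per referral. These figures are illustrations resting on assumed consent, attendance and call effect, not estimates. The point is modest, but it bears on a primary outcome and is cheap to address.

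**What to change.** Keep overall uptake as the headline, and state it as patients completing a WNP appointment divided by patients referred, correcting the inverted ratio. Add two breakdowns:

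1. Uptake for patients referred while research recruitment was open, and for those referred after it closed.
2. Among scheduled patients, appointment completion by called versus not called, taken from the research call log.

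Describe both as descriptive, not as estimates of the call's effect: period is confounded with program start-up, and those who consent are self-selected. State in the Recruitment section whether calls end when the 30th participant consents.

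The cost is one linkage of the call log to appointment status, and smaller denominators with wider intervals in each split.

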### Intervention

The WNP model draws on principles of the collaborative care model (CCM), (Woltmann *et al*., 2012; Miller *et al*., 2013; Press *et al*., 2017) personalized medicine (Yanovski & Yanovski, 2018), and population health management(Neuwirth *et al.*, 2007) to enhance the delivery of team-based, patient-centered, outcome-driven obesity care. Figure 1 shows a conceptual overview of the WNP, which is described in detail below.

**Figure 1. f1:**
[figure not shown]
Weight Navigation Program (WNP) design. Patients with obesity and ≥1 weight-related condition who desire to lose weight are referred by their primary care providers (PCPs) to the WNP. The Weight Navigator and patient develop a personalized obesity treatment plan using existing health system, community, and pharmacotherapeutic resources. The plan is communicated to PCPs via the Electronic Health Record (EHR). Patients self-report weight data using an EHR-based text messaging platform. The WNP team is notified of patients’ weight changes according to pre-specific thresholds. The WNP Care Manager initiates tailored outreach to support patients over time, address potential barriers, and facilitate changes to the treatment plan, if needed, to optimize patients’ outcomes.

Eligible patients who desire to lose weight may be referred to the WNP by their PCP. Referral orders will be reviewed by a clinical scheduler who will confirm patient eligibility, contact patients to schedule an appointment, and send patients a pre-visit weight history questionnaire via the patient Electronic Health Record (EHR) portal in advance of their appointment; weight history questionnaire topics are shown in Table 2. To ensure the Weight Navigator has access to relevant clinical data at the time of the WNP encounter, the referral order will prompt PCPs to obtain a comprehensive metabolic panel, complete blood count, hemoglobin HA1c, fasting glucose, fasting lipid panel, and thyroid function tests.

**Table 2. tbl2:** Weight history questionnaire topics

Birth history and birth weight Weight changes over time (eg, highest and lowest weights) Food frequency assessment (eg, frequency of eating fast food, processed food, high-fat food, sweets) Eating patterns and timing (eg, number of meals and snacks per day binge eating, night eating) Eating triggers Monthly food budget Prior weight loss successes and challenges Physical activity habits

MPOTA-WM participants will be asked to self-weigh at least once per week and report their weight data via text message. Participants without access to a home scale will be provided with one by the study team. Participants will be asked to use the same scale throughout the duration of the study. Participants will self-select the day(s) of the week and time of the day to receive the following text message: ‘Hello, this is your Weight Navigation Program Research Team. What was your weight in pounds today? Reply STOP to opt out of receiving messages from our team’. The WNP team will receive inbox notifications based on the following parameters, which have been adapted from prior literature (Baer *et al*., 2020): (1) weight gain of ≥ 3 pounds at any point; (2) weight loss of varying thresholds (eg, 3%, 5%, and 10% body weight loss); (3) non-response to MPOTA for weight management messages for 14 days; and (4) participants’ ‘STOP’ responses, indicating that they are discontinuing their participation in the text messaging program. The research project manager will initiate tailored outreach; those losing weight, for example, will receive a supportive EHR portal message while those gaining weight will receive a phone call to discuss barriers to weight management, individuals’ preferences and needs, and other available weight management options, as detailed in the WNP encounter note. Communication will be documented in the EHR and patients’ primary care, WNP, and/or weight management subspecialty providers will be alerted, as appropriate.

### Outcome measures

We have 4 outcome categories: (1) feasibility and acceptability of the WNP; (2) clinical impact of the WNP; (3) feasibility, acceptability, and preliminary effectiveness of adding remote weight monitoring by text messaging to the WNP; and (4) feasibility and acceptability of research processes including recruitment and data collection.

#### Feasibility and acceptability of the WNP

Consistent with recommendations for conducting pilot studies (Eldridge *et al.*, 2016), our primary outcomes will be measures of feasibility (ie, extent to which an innovation can be successfully used in a given setting) and acceptability (ie, stakeholder perception that an innovation is satisfactory). Measures of WNP feasibility will include rates of (1) referral (ie, number of patients referred to the WNP divided by the number of patients eligible for the program, as determined by data extraction from the EHR) and (2) uptake (ie, number of patients referred to the program divided by the number of individuals who complete a WNP appointment).

We will assess WNP intervention acceptability through semi-structured interviews with a purposive sample of WNP research program participants to explore individuals’ experiences with the program and solicit feedback on opportunities for improvement. We will also survey primary care providers and patients regarding their satisfaction with the program and solicit feedback on opportunities for improvement.

#### Clinical impact of the WNP

##### Change in weight

We will abstract weight and height data from the EHR for all WNP patients who complete a clinic visit within the first 12 months of clinical program operations. We will evaluate average weight change among WNP patients during the 12 months following their WNP appointment. We will also identify a contemporaneous cohort of patients with obesity matched by gender and approximate age (within 10 years) to WNP patients. The matched cohort will be selected from another Michigan Medicine primary care clinic located less than 1 mile from the pilot site clinic and serving a similar patient population. We will compare between-group weight change among WNP patients and the matched cohort. In addition to evaluating mean weight change, we will also evaluate achievement of ≥5% body weight loss.

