**Methods::**

Quality improvement program with an embedded, 12-month, single-arm pilot study. Patients with obesity and ≥1 weight-related co-morbidity may be referred to the WNP by PCPs. All patients seen within the WNP during the first 12 months of clinical operations will be compared to a matched cohort of patients from another primary care site. We will recruit a subset of WNP patients (*n* = 30) to participate in a remote weight monitoring pilot program, which will include surveys at 0, 6, and 12 months, qualitative interviews at 0 and 6 months, and use of an electronic health record (EHR)-based text messaging program for remote weight monitoring.

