Little is known about the potential weight loss effectiveness of a collaborative care approach to obesity treatment (Ma *et al*., 2019; Lv *et al*., 2020). Prior work testing a collaborative care approach for patients with depression and obesity demonstrated modest weight loss at 12 months, though the majority of participants did not achieve clinically significant weight loss (Ma *et al*., 2019; Pagoto *et al*., 2013). Suboptimal weight loss may have been due, in part, to use of a one-size-fits-all lifestyle change program rather than personalized obesity treatment and follow-up plans (Lv *et al*., 2020).

Our team aims to develop and pilot test an innovative care model – the Weight Navigation Program (WNP) – to integrate Diplomates into primary care settings, enhance delivery of personalized obesity treatment, and successfully help more patients to achieve ≥5% body weight loss (versus traditional care models) while reducing burden on individual PCPs. The aim of this paper is to describe the design, rationale, and planned evaluation for the WNP. We hypothesize that the program will be feasible and acceptable among patients and providers. We also hypothesize that patients who engage in the WNP will achieve greater weight loss than a contemporaneous matched cohort of patients from another primary care clinic with similar sociodemographic characteristics.

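### The weight comparison sets motivated, referred visit-completers with a comorbidity against controls chosen only on obesity, gender and age, so selection cannot be separated from programme effect

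*Protocol article*

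**What the plan says.** Under Clinical impact of the WNP, Change in weight, the protocol article abstracts weights for "all WNP patients who complete a clinic visit within the first 12 months" of the programme and follows each patient for 12 months from the WNP appointment. The abstract agrees: "All patients seen within the WNP during the first 12 months of clinical operations will be compared to a matched cohort".

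Other sections show how a patient reaches that group. Study design requires a wish to lose weight and a PCP referral. Participants WNP eligibility requires BMI ≥30 and at least one weight-related chronic condition, and excludes pregnancy and breastfeeding. The patient must then complete the one-hour visit described under Intervention.

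The comparator is a "contemporaneous cohort of patients with obesity matched by gender and approximate age (within 10 years) to WNP patients", "selected from another Michigan Medicine primary care clinic located less than 1 mile from the pilot site clinic and serving a similar patient population". The article gives no further condition and no start date for controls.

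Quantitative data analysis specifies a difference-in-difference approach for weight and counts of patients with ≥5% loss at 6 and 12 months.

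The Background gives two statements of purpose. The aim is that the model should "successfully help more patients to achieve ≥5% body weight loss (versus traditional care models"). The hypothesis, in the same paragraph, is narrower: patients who engage in the WNP will lose more weight than the matched cohort.

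**The concern.** The two groups are selected by different rules, and the differences bear on the outcome. Wanting to lose weight, being referred for it and keeping a long weight-focused appointment plausibly go with a different weight course over the next year, whatever the programme does. A weight-related condition may do so too. None of these features is required of controls or matched on.

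The result is reported as the clinical impact of the WNP. Under Future directions it also informs preliminary weight-loss effectiveness ahead of a large pragmatic trial. If part of the contrast is selection, that trial could be planned on a misleading effect, and readers could take the pilot as evidence for the programme-level aim.

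**Working it through.** **1. Entry conditions side by side, as stated in the article**

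| Condition | WNP group | Matched cohort |
|---|---|---|
| Obesity | Yes, BMI ≥30 | Yes |
| ≥1 weight-related condition | Yes | Not stated |
| Not pregnant or breastfeeding | Yes | Not stated |
| Wish to lose weight | Yes | Not stated |
| PCP referral | Yes | Not applicable as stated |
| Completed index visit | Yes (WNP appointment) | Not stated |
| Start of follow-up | WNP appointment | Not stated beyond contemporaneous |
| Gender, age within 10 years | Matched | Matched |

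**2. What difference-in-difference removes**

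Difference-in-difference = (mean change in WNP group) − (mean change in controls) = programme effect + (difference in mean change that would have occurred without the programme).

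A constant gap in weight level cancels. The second term is zero only if both groups would have followed the same course untreated. The unmatched rows above are reasons why they might not. The ≥5% outcome is defined on change from baseline, so it is exposed to the same term.

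**3. Is there a figure in the plan to reproduce?**

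The article gives no SD, significance level, power, matching ratio or attendance rate for this comparison. Its one relevant number is the capacity estimate of about 150 patients in year 1 (Recruitment). At 4 per session that is 150 / 4 = 37.5 sessions, against a ceiling of 4 × 52 = 208 patients; the figure is plausible.

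**4. Illustration under assumed inputs**

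Suppose the programme has no effect. Let *d* be the extra 12-month loss that attender-type patients would have without it, and *m* the share of such patients among controls. Then

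spurious difference = (1 − *m*) × *d*.

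- Low end: *d* = 1 kg, *m* = 0.5 gives 0.5 × 1 = 0.5 kg.
- Middle: *d* = 2 kg, *m* = 0.3 gives 0.7 × 2 = 1.4 kg.
- High end: *d* = 3 kg, *m* = 0.1 gives 0.9 × 3 = 2.7 kg.

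For scale, assume 150 per group (1:1 matching) and an SD of change of 6 to 8 kg. The standard error is 6 × √(2/150) = 0.69 kg to 8 × √(2/150) = 0.92 kg. The shift then runs from 0.5 / 0.92 = 0.5 to 2.7 / 0.69 = 3.9 standard errors.

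**5. The part due to attendance alone**

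If a share *u* of referred patients completes the visit, and non-completers would have lost *d* less regardless, the completers' mean exceeds the all-referred mean by (1 − *u*) × *d*:

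- *u* = 0.8, *d* = 1 kg: 0.2 kg.
- *u* = 0.6, *d* = 2 kg: 0.8 kg.
- *u* = 0.4, *d* = 3 kg: 1.8 kg.

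This is the gap between completers and all referred patients. It is not the bias against controls, who differ in more than attendance.

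**The case against.** The strongest reply is that the analysis set is deliberate. The hypothesis concerns patients who engage, so leaving out non-attenders defines the target population. The aim of helping more patients reach ≥5% loss describes what the care model is for. This stands: restricting the WNP group to completers is not an error. It does not answer the comparator problem, because an effect in engagers needs controls who resemble engagers.

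A reader might infer that the plan demonstrably inflates the WNP result. The documents do not support that. PCPs may refer patients whose weight is hardest to manage, and the Intervention section expects to find obesogenic drugs and conditions that hinder weight loss. That would work against the WNP. A reader might also want a false-positive rate, but the article states no significance rule for this contrast, and any such rate would rest on assumed inputs.

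It can also be said that this is a condensed article and that a sensitivity analysis belongs in a fuller document. That is fair for the companion analysis, and an index date for controls might be given there too. But the article itself fixes the analysis set and the matching factors, and those are what is questioned. Its limitations do not mention selection, but the numbering there skips from the second item to the fourth, so little should be made of that silence.

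Finally, weight change is not primary; feasibility and acceptability are. This limits the consequences and stands.

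**Conclusion.** The point holds as a comparability problem. As stated, the contrast mixes programme effect with selection on weight-loss intent, referral, comorbidity and attendance, for both mean weight change and ≥5% loss, and difference-in-difference does not separate them. Bias in favour of the WNP is likely but unproven.

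Its size cannot be derived from the documents. The 0.5 to 2.7 kg range assumes no programme effect, *d* of 1 to 3 kg and *m* of 0.1 to 0.5. It shows only that a shift of the same order as the standard error is possible.

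Two stronger conclusions should not be drawn: that the visit-completer analysis is wrong for its hypothesis, or that an all-referred analysis would by itself remove the bias. All referred patients are still selected on intent and referral. The primary outcomes are unaffected, but the change is worth making because it is cheap and the estimate feeds a later trial.

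**What to change.** 1. Keep the visit-completer analysis for the hypothesis about patients who engage.
2. Require controls to meet the WNP eligibility criteria: BMI ≥30, at least one weight-related condition, not pregnant or breastfeeding. Require an index primary care visit with a recorded weight in the same calendar period, and start their follow-up there.
3. Add a companion analysis of all patients referred in the first 12 months, attended or not, with follow-up from the referral date. Report mean change and ≥5% loss for both analyses.
4. Describe both contrasts as associational, since selection on weight-loss intent and referral remains. Do not claim a programme-level benefit from the visit-completer contrast alone.

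The cost is small. The uptake measure, "number of patients referred to the program divided by the number of individuals who complete a WNP appointment", already needs the lists of referred patients and completers, and the weights come from the same EHR. The downsides are a diluted, less favourable estimate and possibly more missing weights among non-attenders, so the number with a usable weight should be reported for each group.

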### Study design

This is a clinical quality improvement project with an embedded single-arm pilot study. Specifically, patients with obesity who desire to lose weight will be referred by their PCP to the WNP. Patients scheduled for a WNP appointment will be offered the opportunity to participate in research; we will aim to recruit 30 participants to the research arm of the study Research activities include (1) surveys at 0, 6, and 12 months; (2) optional semi-structured interview participation at 0 and 6 months; and (3) use of a text messaging program for remote weight monitoring.

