### Participants WNP eligibility

Primary care patients with a body mass index (BMI) ≥ 30 kg/m^2^ and at least one weight-related chronic condition (eg, type 2 diabetes, hypertension, hyperlipidemia, non-alcoholic fatty liver disease, obstructive sleep apnea) may be referred by their PCP to the WNP. WNP exclusion criteria include primary care received at a location other than the pilot clinic site and pregnancy or breastfeeding. Patients may be scheduled for a WNP appointment regardless of insurance type. However, patients’ eligibility and out-of-pocket costs for obesity treatments may differ based on insurance status; this will be taken into consideration by the Weight Navigator when working with patients to develop personalized treatment plans.

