### Data analyses

#### Quantitative data analysis

Measures of central tendency (eg, proportions, means, standard deviations) will be used for all descriptive analyses. We will calculate mean 3-month and 6-month weight changes from baseline. We will also calculate the number of participants that achieve ≥5% body weight loss at 6 and 12 months. We will compare between-group changes (ie, all WNP participants versus WNP research participants and all WNP participants versus matched cohort) in weight using a difference-in-difference analytic approach. Among WNP research participants, we will also calculate mean weight change based on MPOTA-WM data. We will conduct all analyses using Stata 15.

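### The matched cohort is chosen on obesity, gender and age alone, so the weight comparison with WNP patients is open to selection confounding of unknown net size

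*Protocol article*

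**What the plan says.** **Comparator.** Under Clinical impact of the WNP, Change in weight, the team will "identify a contemporaneous cohort of patients with obesity matched by gender and approximate age (within 10 years) to WNP patients". These patients come from one other clinic, "located less than 1 mile from the pilot site clinic and serving a similar patient population". No other matching variable or entry rule is given.

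**WNP group.** Participants WNP eligibility requires a BMI of at least 30 kg/m² "and at least one weight-related chronic condition", and excludes "pregnancy or breastfeeding". Study design adds that "patients with obesity who desire to lose weight will be referred by their PCP to the WNP". The weight analysis then takes "all WNP patients who complete a clinic visit within the first 12 months of clinical program operations".

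**Analysis and hypothesis.** Quantitative data analysis compares changes "in weight using a difference-in-difference analytic approach". The Background states the hypothesis that "patients who engage in the WNP will achieve greater weight loss than a contemporaneous matched cohort". The comparisons of referrals, engagement, prescriptions and refills use the same matched cohort.

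**Status.** Feasibility and acceptability are the primary outcomes. The limitations section covers the single site, treatment cost and reliance on research funding. It does not mention whether the two groups are comparable.

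**The concern.** The article names its matching variables, so this is a rule that is stated and works poorly, rather than a detail deferred to another document. Applied as written, it sets a selected subset of one clinic (with a comorbidity, wanting to lose weight, referred and attending) against patients of another clinic who need only have obesity and be of the same gender and similar age.

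Wishing to lose weight, being referred and turning up can each affect how weight changes over the following year, with or without the programme. A weight difference at 12 months could then reflect who was selected as well as what the programme did.

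At stake is one of the article's two stated hypotheses. The comparison is also its only external evidence of preliminary effectiveness ahead of the larger pragmatic trial described under Future directions.

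**Working it through.** **Step 1: entry rules side by side.**

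| Criterion | WNP patients | Matched cohort, as stated |
|---|---|---|
| Obesity | BMI ≥30 kg/m² | Obesity |
| Weight-related condition | At least one | Not required |
| Pregnancy or breastfeeding | Excluded | No rule stated |
| Wish to lose weight | Required | Not required |
| PCP referral | Required | Not applicable |
| Attendance | Completed WNP visit | Not required |
| Gender | – | Matched |
| Age | – | Within 10 years |
| Baseline BMI or weight | – | Not matched |

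The groups agree on obesity, gender and approximate age. They differ on five criteria that define the treated group, and are not aligned on baseline BMI.

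**Step 2: do the stated safeguards close the gap?**

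- *Nearby clinic with a similar population.* This is similarity between clinics. The WNP group is a selected part of its clinic, while the comparator is drawn from everyone with obesity at the other.
- *Difference-in-difference.* This subtracts any constant difference in weight between groups. It identifies a programme effect only if both groups would have followed parallel weight trends without the programme. Selection on motivation, referral and attendance bears on the trend itself.

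**Step 3: direction.** Motivation and referral plausibly favour WNP. The comorbidity requirement could act either way. The article itself mentions, under Intervention, obesogenic medications and co-morbidities that may hinder weight loss. The net direction and size are therefore unknown.

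**Step 4: illustration under assumed values.** The article gives no SD, alpha, matching ratio or power for this comparison, so there is no stated figure to reproduce. The 150 is its estimate of WNP patients seen in the first year. Everything else is assumed: 1:1 matching, SD of 12-month percent weight change 6–8 points, two-sided 0.05, zero programme effect, and a selection-driven difference b.

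SE = SD × √(2/150), which is 6 × 0.1155 = 0.69 or 8 × 0.1155 = 0.92.

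P(significant) = Φ(b/SE − 1.96) + Φ(−b/SE − 1.96)

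| b (points) | SD 6 | SD 8 |
|---|---|---|
| 1 | 0.30 | 0.19 |
| 2 | 0.82 | 0.58 |
| 3 | 0.99 | 0.90 |

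The nominal rate is 0.05.

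**Step 5: the same idea for ≥5% loss.** Assume that, without any programme, 25% of patients who wish to lose weight and 10% of the others reach 5%. Assume also that 30–70% of comparators wish to. The spurious difference is 0.25 − [0.25s + 0.10(1 − s)] = 0.15 × (1 − s), where s is that share. This is 10.5 percentage points at s = 0.3 and 4.5 at s = 0.7. With 150 per group, the chance of a false significant result is about 0.63 and 0.15.

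**The case against.** The other side has real points.

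- **The bias is assumed, not shown.** The illustration is driven almost wholly by the b that is put in. It shows what a given bias would do and is no evidence that one of that size exists. This stands.
- **Parallel trends is not proven false.** A reader might infer that it must fail because patients are referred at a weight peak and then regress to the mean. The article does not support this: it says only that eligible patients may be referred, and nothing about their weight history. Doubtful is the right word.
- **The effect on the other comparisons is limited.** A reader might infer that comparators broadly qualify for fewer resources. Table 1 gives a comorbidity requirement for only one treatment programme, Obesity & Metabolic Disorders, and no BMI cut-off for any. The referral, engagement and medication comparisons share the selection problem, but a general eligibility gap is not documented.
- **Some detail may sit elsewhere.** Index dates, covariate adjustment and trend checks may be in a fuller document, and their absence here is not a fault. The matching rule itself is stated, so the point does not depend on them.
- **The fix is partial.** Motivation, referral and attendance will remain unmatched. This is true, and is why the result also needs a label and a stated limitation.
- **This is a pilot.** The weight comparison is not primary, the article calls the effectiveness evidence preliminary, and no go/no-go decision is tied to it. This lowers the urgency, not the validity, of the point.

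**Conclusion.** The concern holds as a risk of confounding. The stated comparator rule leaves out WNP entry criteria that can be checked in the EHR and does not align baseline BMI, while WNP patients are further selected on motivation, referral and attendance. Neither the neighbouring clinic nor difference-in-difference removes differences in trajectory. As planned, the comparison cannot separate programme effect from patient selection.

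The net size is unknown. The percentages in the illustration hold only under its assumed SD, alpha, 1:1 ratio and selection difference. A reader might conclude that the result is known to be biased towards WNP, but the article does not support that, because the comorbidity requirement could pull the other way.

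This should be fixed before the analysis. It is not a reason to hold up the pilot, whose primary outcomes are feasibility and acceptability.

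**What to change.** 1. Apply the EHR-checkable WNP criteria to the comparison clinic: BMI ≥30, at least one weight-related condition, not pregnant or breastfeeding. The article already plans an EHR extraction to count eligible patients for the referral rate, and the same query can be run at the second clinic.
2. Give each comparator an index primary care visit with a measured weight, close in calendar time to its match's WNP visit.
3. Match on or adjust for baseline BMI and type 2 diabetes, as well as gender and age.
4. Where earlier EHR weights exist, show weight trends before the index date in both groups. The article does not say how complete these weights are, so this step depends on availability.
5. Report the weight, referral, engagement and medication comparisons as associational, and add residual selection by motivation, referral and attendance to the limitations.

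**Cost.** More query and matching work, with no extra patients or visits. A few WNP patients may lack a match. Steps 1–4 reduce the mismatch but cannot remove selection on motivation, referral or attendance, so step 5 is needed in any case.
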